## Methods/Design

### Study design

The Diabetes and Mindfulness (DiaMind) study will be conducted as a randomized controlled trial (RCT). Dutch speaking patients with DM with low levels of emotional well-being recruited from outpatient diabetes clinics will be randomly allocated to the intervention group or the wait-list (usual care) control group. The intervention group will receive the mindfulness program immediately, while the control group will receive the program eight months later (six months after the training of the intervention group).

### Eligibility

We will include adult men and women (aged 18 - 80 years) who were diagnosed with diabetes (type 1 or 2) and have poor emotional well-being as evidenced by a score of < 13 on the WHO-5 well-being Index [34]. Patients will be excluded when they have a recent history of severe psychopathology (i.e., psychosis, risk of suicide attempts); or alcohol/drugs abuse; have a severe physical co-morbidity (i.e., severe forms of cancer or heart failure); when they have insufficient reading and comprehension skills of the Dutch language; when they are already in an (extensive) psychological treatment which started within a period of 6 weeks before the start of the training; and when they already have meditation experience (with Vipassana, Zen, or Dzogchen).

### Recruitment and screening process and enrolment

The recruitment of patients will take place in outpatient diabetes clinics. At present, internists of the outpatient clinic of the Maxima Medical Center (Veldhoven and Eindhoven), the Catharina Hospital (Eindhoven) and the TweeSteden Hospital (Tilburg) have agreed to participate. Depending on the preferences of the diabetes teams in the participating hospitals, the screening will be conducted by the internists, diabetes nurses or by a researcher of our team. The screening tool will be the WHO-5 well-being Index [34]. This short (5-item) screening instrument, which assesses emotional well-being, is validated in the general population, but also in different patient samples, including patients with type 1 diabetes [35] and is recommended for use by the International Diabetes Federation (IDF) [14]. If patients have a low score on this scale (<13) they will receive an information letter about the training and study. One week later these patients will be telephoned and asked whether they are interested to participate in the project.

Eligible patients who are interested to participate will be invited for a short interview. This interview will take place in the hospital or, if logistically difficult for the patient, at their home. During this interview the in- and exclusion criteria will be checked once again, and expectations of the patient about the training will be checked and if necessary adjusted. Eligible patients will receive a written informed consent form during the interview that has to be signed and returned before the start of the training. Furthermore, at the end of the interview the blood pressure of the patients will be measured. If blood pressure is elevated (≥140/90 mmHg) the patient will be attached to an ambulatory blood pressure device which will measure blood pressure the following 24 hours. One day later the device will be brought back to the hospital by the patient or be picked up at the patient's home by a researcher.

### Randomization

After the inclusion of every 16 to 20 patients the participants will be randomized into two groups: the intervention group and the control group. The randomization will be done as follows. After the interview and upon receipt of a signed informed consent form, the patient will be assigned to a participant number. Subsequently the participant will receive the baseline questionnaire by mail or email. When the first author receives the baseline assessment, she passes on the corresponding participant number to the second author who has no further involvement in the practical recruitment, enrolment, and assessment of the patients. The second author will refer to the computer generated (through PASW Statisitics 17) random list (uneditable and concealed for others) prepared by a statistician with no involvement in the trial. The second author will inform the first author about the allocation by email and will archive the allocations in a secured document on his computer. The first author will document the allocation in the general inclusion database, which will be checked by the second author. The first author will inform the patients both by telephone and letter about their allocation. The above described procedure will eliminate experimenter bias in group assignment. The computer program the statistician will use utilizes a random number generator and will be programmed to insure equal numbers of subjects in each arm of the study within a block of 4 participants.

### Masking

The nature of this psychological intervention does not allow "masking" or blinding of patients, and trainers. However, the statistician who will be involved in data analyses will be blinded for treatment allocation. All the questionnaires and homework forms will only be marked with a participant number, which is unknown to the trainer and researcher.

### Intervention

#### Training

The protocolised mindfulness training is based on the Mindfulness-Based Stress Reduction and Mindfulness-Based Cognitive Therapy programs as described in Kabat-Zinn [28] and Segal et al. [36], consisting of eight weekly two-hour sessions. A few modifications have been made to the original protocol and the workbook in order to make the intervention suitable for patients with diabetes. For example, the trainers explain the potential associations between emotional problems and diabetes management and diabetes outcomes (e.g., the associations between emotional stress and eating behaviors will be discussed). Instead of the silent day that is part of the original program, a two-hour booster session has been added three months after the end of the intervention. At each session the participants will receive homework assignments that take about 30 minutes 5 days per week. All the sessions will be supervised by certified psychologists who have at least four years practical experience with mindfulness, and also completed a mindfulness instructors training of eight days in The Netherlands. The standard format of the sessions is as follows: the session starts with an exercise, which is followed by a discussion about the exercise and the homework exercises of the preceding week. Subsequently, a discussion about the theme of the session takes place, followed by the administration and discussion of one or two other mindfulness exercises. Finally, the homework assignments of the following week are discussed. All sessions end with a short meditation and/or a relevant poem or story.

##### Session 1

The first session of the course will consist of: 1) an invitation to all participants to introduce themselves sequentially, 2) a brief overview of the coming eight weeks, 3) a discussion about the relationship between diabetes, diabetes management, diabetes outcomes and emotional distress. After this, participants will be invited to slowly and mindfully eat a raisin with all their senses (the raisin exercise), which will be followed by a discussion about the fact that many people live their lives in a unmindful way, often do not pay much attention to what they are doing. Subsequently, the participants will be led through a body scan exercise of thirty-five minutes, during which the participants are encouraged to focus on the physical sensations in different body parts and to bring their attention back to that focus when they get distracted from it by thoughts or other momentary phenomena. At the end of the first session the participants will receive a CD containing several exercises and will be asked to practice the bodyscan on five occasions in the following week. In addition, they will be advised to perform one daily activity (e.g. to wash the dishes, to brush their teeth) in a mindful way and to eat one meal per day mindfully.

##### Session 2

At the beginning of the second session the participants will be guided again through the body scan, after which they will be invited to express and share their experiences with the mindfulness exercises and the homework of the preceding week. Subsequently there will be a discussion about coping with obstacles to doing the exercises (e.g., irritation, wandering mind) and attitudes that support the cultivation of mindfulness (e.g., not judging, letting go). After that, participants will be led through an exercise 'thoughts and feelings', which explains a basic component of cognitive behavioral therapy: our emotions are not caused by events but by our perception of events. Subsequently, the participants will practice 'sitting meditation', with breathing as the primary object of attention. Home practice for the following week will include awareness of pleasant events, a new routine daily activity, the bodyscan, and brief sitting meditation.

##### Session 3

The third session will start with a short 'Seeing and/or hearing exercise', in which participants are instructed to exercise non-judgmental seeing or hearing for a couple of minutes. This exercise will be followed by a sitting meditation with focus on breathing and bodily sensations. After the homework discussion, there will be a talk by the trainer about attention to breathing, followed by the practice and discussion of the '3-minute breathing space'. This meditation has three phases: attention to the experiences in the moment, attention to the breathing, attention to the body. Subsequently, an exercise in mindful body movements will be introduced and discussed. Exercises to be practiced during the following week will include sitting meditation, bodyscan or body movement exercises, 3-minute breathing space, new mindful daily activity, and awareness of unpleasant events.

##### Session 4

The fourth sessions will start with a sitting meditation with attention to the breathing, the body, sounds, and thoughts (so called 'sitting meditation with four focuses'). Subsequently, there will be a discussion about the stress response and common reactions of individuals to difficult situations, and alternative attitudes and reactions will be discussed. Then a Dutch documentary about MBSR (entitled 'Aandachttraining') will be shown to the participants. At the end of the session an exercise in mindful walking will be introduced and practiced. The homework assignments for this fourth session will consist of practicing sitting meditation, the bodyscan or mindful body movements, 3-minute breathing space (also during unpleasant events), to fill in the questionnaire 'automatic thoughts' (optional), and to read an inspiring book about mindfulness (optional).

##### Session 5

At the beginning of the fifth session the participants will be guided through the sitting meditation with four focuses (see Session 4). A poem will be read and the psychologist will discuss the theme of the fifth session: 'Acknowledging and accepting the reality of the present situation as it is.' Subsequently, the second series of mindful body movements will be introduced. The recommended home work will consist of sitting meditation, 3-minute breathing space, 3-minute breathing space during unpleasant events, and a new daily activity performed mindfully.

##### Session 6

The sixth session will begin with the 3-minute breathing space. The homework assignments will be discussed mindfully in pairs. An exercise called 'mood, thoughts, and different view points' will be discussed plenary, as well as the theme of the sixth session: 'The content of our thoughts is (often) not factual'. Subsequently, the participants will be guided through four linked up meditation exercises, with a total duration of one hour. For the following week participants will be encouraged to choose a combination of meditations that fits their needs and personal preferences. In addition, the home practice includes the 3-minute breathing space (also during unpleasant events), a new mindful daily activity, and having a mindful conversation while paying attention to one's automatic patterns (optional).

##### Session 7

The seventh sessions will start with the meditation exercise with four focuses and open awareness (to whatever enters consciousness from moment to moment). The theme of the session, 'What is the best way to care for oneself', will be discussed, followed by an exercise during which participants explore daily activities that are pleasant versus unpleasant and learn to plan sufficient pleasant activities. The 3-minute breathing space is performed, followed by a loving-kindness meditation during which one practices kindness towards oneself and others. The home practice includes a meditation combination of one's choice, 3-minute breathing space (also during unpleasant events), a new daily activity performed mindfully, and filling in a form including warning signals for emotional distress.

##### Session 8

The session will begin with a body-scan. The theme of the last session will be discussed: 'Using what you have learned'. Subsequently the psychologist will guide the participants through a 3-minute breathing space and will read a story called 'Five chapters', which is about the steps one can take to overcome our pitfalls in the practice of mindfulness. Finally, the whole training will be evaluated with the participants. For example the following questions will be asked: did the training meet their expectations, do participants have a sense of 'personal growth', do they feel that they have expanded their coping skills and do they want to continue practicing mindfulness. In addition, resources for continued practice will be given (e.g. titles of books and addresses of local meditation centers).

### Evaluation

After completing the training the patients will be invited for a short interview, in which the patient's perceptions regarding the quality of the intervention will be evaluated and the procedure with the ambulant blood pressure measurement will be repeated.

### Data collection

Table 1 shows the assessment instruments and data collection time points. Assessments will take place before the start of the intervention, at 4 weeks, at 8 weeks (= post intervention), at 12 weeks and at 34 weeks (6 months post intervention). The control group will receive another four measures, namely at 38 weeks (4 weeks after start of control group intervention), at 42 weeks (post control group intervention), at 46 weeks, and at 62 weeks (6 months post control group intervention). Process variables (e.g., attendance, adherence, and drop-out) will be collected continuously. The patients who have access to the internet and email will receive the questionnaire via the internet. If this is not the case, they will receive a paper version of the questionnaire along with a stamped addressed envelope.

**Table 1 T1:** Measurements and time points

Concept	Questionnaire		Measurement time points							
		
		T1	T2	T3	T4	T5	T6	T7	T8	T9
Perceived stress	PSS (14)*	**x**	**x**	**x**		**x**	x	x		x

Anxiety and depressive symptoms	HADS (14)	**x**	**x**	**x**		**x**	x	x		x

Mood	POMS (32)	**x**	**x**	**x**		**x**	x	x		x

Diabetes related problems	PAID (20)	**x**	**x**	**x**		**x**	x	x		x

Quality of life	SF12 (12)+3 items WHOQOL	**x**		**x**		**x**		x		x

Self-care behavior	ADSCI (11)	**x**		**x**		**x**		x		x

Extraversion	EPQ-E (12)	**x**								

Type D Personality	DS14 (14)	**x**		**x**		**x**		x		x

Mindfulness	FFMQ(31)	**x**		**x**		**x**		x		x

Diabetes related mindfulness	AADQ (11)	**x**		**x**		**x**		x		x

Self-esteem	RSES (10)	**x**		**x**		**x**		x		x

Patient's background (demographics, clinical, psychological)	- (21)	**x**								

**Clinical measurements**	**Measurement**									

Glycemic control (from hospital database)	hbA1c	**x**			**x**	**x**			x	x

Blood pressure	Amb.24 h BP	**x**		**x**						

T1 - baseline; T2 - after 4 weeks of intervention; T3 - after 8 weeks (post intervention); T4 - after 12 weeks (4 weeks post intervention); T5 - after 8 months (6 months post intervention = start training for control group). T6 thru T9 only for control group: repetition of T2 thru T5. PSS - Perceived Stress Scale; HADS - Hospital Anxiety and Depression Scale; POMS - Profile of Mood States; PAID - Problem Areas in Diabetes Survey; SF-12 - Short Form Health Survey; 3 items WHOQOL-bref^9^; ADSCI - Amsterdam Diabetes Self Care Inventory; EPQ-E - Eysenck Personality Questionnaire subscale Extraversion; DS14 - Type D personality scale; FFMQ - Five Factor Mindfulness Questionnaire; AADQ - Acceptation and Action Diabetes Questionnaire; RSES - Rosenberg Self-esteem Scale. HbA1c = hemoglobin A1c (the amount of glycated hemoglobin in blood). Amb. 24 h BP = Ambulatory 24 hour Blood Pressure monitoring.

*= number of items in questionnaire. Total number of items = 205.

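### The last control-group assessment (T9) is dated week 62 and labelled six months after training, but the article's own dates and the Table 1 legend both give week 68

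*Protocol article*

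**What the plan says.** The Data collection section gives the intervention schedule as assessments before the start, at 4 weeks and then "at 8 weeks (= post intervention), at 12 weeks and at 34 weeks (6 months post intervention". The control group has four further assessments: "at 38 weeks (4 weeks after start of control group intervention", then "at 42 weeks (post control group intervention", and finally "at 46 weeks, and at 62 weeks (6 months post control group intervention".

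The legend to Table 1 ties the two schedules together. It defines "T5 - after 8 months (6 months post intervention = start training for control group", so control training begins at week 34. It then states "T6 thru T9 only for control group: repetition of T2 thru T5". The Study design section agrees on the delay: "the control group will receive the program eight months later (six months after the training of the intervention group".

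In Table 1, T9 carries the PSS, HADS, POMS and PAID, which are all the instruments listed as primary outcome measures. It also carries the quality-of-life, self-care, mindfulness, self-esteem and Type D questionnaires, and HbA1c. Ambulatory blood pressure is not measured at T9.

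**The concern.** One sentence gives T9 both a week number and a description, and the two do not agree. The description can be checked because the article fixes the end of control training and shows, in the intervention arm, how many weeks it counts as six months. The legend's repetition rule is a second check.

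T9 is the only assessment of longer-term maintenance in the control group after its own training. If questionnaires were sent at week 62, a result reported as six-month follow-up would be a 20-week result. Anyone who set it beside the intervention arm's T5, or pooled the two, would be combining 20 weeks with 26 weeks of follow-up.

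**Working it through.** **Inputs, all from the Data collection section and the Table 1 legend**

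- End of intervention training (T3): week 8.
- Six-month follow-up in the intervention schedule (T5): week 34.
- Start of control training: T5, so week 34.
- End of control training (T7): week 42.
- T9 as stated: week 62.

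**Route 1: the label.** In the intervention schedule, six months = T5 − T3 = 34 − 8 = 26 weeks. Applied to the control group, T9 = T7 + 26 = 42 + 26 = week 68.

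**Route 2: the repetition rule.** Each control date = 34 + the week of the matching intervention assessment.

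| Control assessment | Repeats | By the rule | Stated | Difference |
|---|---|---|---|---|
| T6 | T2 (week 4) | 34 + 4 = 38 | 38 | 0 |
| T7 | T3 (week 8) | 34 + 8 = 42 | 42 | 0 |
| T8 | T4 (week 12) | 34 + 12 = 46 | 46 | 0 |
| T9 | T5 (week 34) | 34 + 34 = 68 | 62 | 6 weeks early |

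The rule reproduces three of the four stated dates exactly. Only T9 fails.

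**Can week 62 be recovered by another reading?** Six months was taken as 24 weeks, 26 weeks or 6 × 365.25/12/7 = 26.1 weeks.

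- Counted from T7 (week 42): 66, 68 or 68.1.
- Counted from the start of control training (week 34): 58, 60 or 60.1.
- Counted from T8 (week 46): 70, 72 or 72.1.
- Eight months doubled: 64 weeks with four-week months, 69.6 weeks with calendar months.

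None gives 62. The shortest reading of the label as written, 24 weeks after week 42, still gives week 66.

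**Size of the gap**

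- Time from end of training to T9: 62 − 42 = 20 weeks, or 20 / (365.25/12/7) = 4.6 months.
- Ratio to the intended interval: 20/26 = 0.77, so 23% shorter.
- T8 to T9: 62 − 46 = 16 weeks, against T4 to T5 of 34 − 12 = 22 weeks.
- The Training section adds a booster session three months after the end of training. Taking that as about 13 weeks, and assuming controls receive the same programme, the booster falls near week 42 + 13 = 55. T9 would then follow it by 62 − 55 = 7 weeks instead of 68 − 55 = 13.

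**The case against.** The arithmetic is hard to dispute, so the case on the other side concerns consequence.

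1. **No stated analysis uses T9.** The hypotheses are comparisons with a wait-list control, the Planned analyses section tests group differences over time, and the abstract places the primary outcome at baseline, four weeks, post intervention and six-month follow-up, which are T1, T2, T3 and T5. This stands. A reader might infer from the parallel schedules that the article plans to replicate the six-month result by setting T9 against T5. It describes no such comparison or pooling, so that harm is conditional.

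2. **HbA1c need not move.** A reader might infer that the last control HbA1c would also come six weeks early. According to the Glycemic control section, the values are routine three-monthly hospital measurements. Moving the target date from week 68 to week 62 might pick up the same measurement or an earlier one. This stands, and the timing argument therefore concerns the questionnaires.

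3. **It may be only a misprint.** The label and the legend both define T9 consistently, and 62 differs from 68 by one digit. The operational mailing schedule is not shown, so a reader who concludes that patients will in fact be assessed at week 62 goes further than the document allows. This stands as well, and so the request is to check the schedule. The booster interval likewise matters only if week 62 is followed.

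These points limit the consequence. They do not make week 62 compatible with its label.

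**Conclusion.** The week number for T9 is wrong by the article's own dates. Week 62 cannot be six months after training that ends at week 42, and it breaks the rule that T6 to T9 repeat T2 to T5. Both routes give week 68, a difference of six weeks.

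The consequence is limited and conditional. If week 62 were followed, the control group's final questionnaires, including all the primary-outcome instruments, would be taken 20 weeks after training and reported as six months. T9 would then not be comparable in timing with the intervention arm's T5, should anyone compare or pool them. The randomised comparison over T1 to T5 is untouched, because T6 to T9 exist only in controls after the allocated waiting period. The sample size does not depend on this date either.

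The conclusion needs only the article's own equation of six months with the interval from week 8 to week 34. It does not depend on whether the figure is a misprint. Because it concerns a date in the assessment schedule and costs one number to correct, it should be corrected.

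**What to change.** Reconcile the T9 week number in the Data collection section with its label and with the Table 1 legend; both imply week 68. Then check that the operational questionnaire schedule uses the reconciled date.

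If some control patients have already been assessed at week 62, report their T9 values as 20-week follow-up, and state the actual interval since training wherever T9 is presented. For HbA1c, report the date of the hospital value used, since its timing is approximate in any case.

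The cost is one number in the text and one check of the schedule. If week 62 was in use, control follow-up ends six weeks later. The Discussion reports 16 patients enrolled with recruitment continuing, so a prompt correction can still govern most T9 assessments.
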